## Randomisation

The four practices will be randomly allocated by the study statistician to receive the standardised PS-PC intervention until all four sites have implemented it. Timing of allocation will depend on the relative needs of the practices and peer worker providers (e.g., staffing, leave arrangements, time of year). At the initialisation of each wedge, staff leaders at the relevant practice site will champion the practical implementation of the PS-PC, beginning with recruitment strategies. All participants will receive usual care, plus the addition of peer support when their study site switches to the PS-PC intervention. Due to the trial’s specific nature, neither randomisation nor blinding of participants will take place. Participants have the freedom to withdraw from the intervention at any time upon their request.

## Recruitment and enrolment

GPs at each enrolled practice will use prospective enrolment and compile a list of people living with mental health conditions currently attending the practice who may benefit from the PS-PC intervention. GPs will introduce the study to potential participants and provide key details. The study will also be promoted within the waiting rooms of participating practices for people living with mental health conditions to self-nominate for eligibility screening. GPs will then screen participants for eligibility and those wanting to participate will be referred to a designated practice nurse to complete informed consent processes. Information about those who choose not to participate at this point will be documented with consent.

## Eligibility criteria

A person will be eligible to participate if they are as follows:18 years of age or olderHave a diagnosis of a mental health condition (or present with symptoms indicating the likelihood of a mental health condition)Attend participating practices (study sites)

A person will be ineligible to participate if they:Have a significant mental health condition or physical illness likely to disrupt their capacity to participate in the trial (as measured by GP assessment of current suicidality risk and/or Kessler psychological distress scale (K10) cut of score of > 40/50)Are unable to speak EnglishAre already receiving peer support through an alternative funded programme

To gain greater understanding of the impact of the trial beyond the participant, a subset of family members or carers will complete the short-form Burden Scale for Family Caregivers (BSFC-s) [30]. Participants who are willing and have a suitable person to nominate will be provided with a consent form, questionnaire, and reply paid envelope to give to a family member or carer. Family members and carers can opt in to be part of the study at this point by either returning the completed forms or following a link to an online version. No inclusion or exclusion criteria apply beyond being nominated by the participant.

Peer workers involved in the study will complete the General Self-Efficacy scale (GSE) to inform intervention efficacy for those providing care. Additionally, a scale will be developed to measure evaluate participating practice staff attitudes toward peer workers. This scale will be informed by the components involved in the Theoretical Framework of Acceptability (TFA) [31]. Peer worker and practice staff participants will be recruited through their employer, with no obligation to be involved and no requirements for inclusion beyond their employment. These participants will be informed about the data collection component of their involvement in the study and will give written consent to participate when completing the forms. Completed forms can be provided to study staff via the study contact representative at their workplace (either the peer coordinator or practice manager) or by following a link to an online version.

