**Fig. 3 Fig3:**
[figure not shown]
Schedule of enrolment, intervention, and assessment (SPIRIT Figure)

A summary of the evaluation schedule, underpinned by the RE-AIM framework is provided in Table 1. Routinely collected data including demographics and diagnosis details will be recorded (with consent) by practice staff through chart auditing the GP records of prospective participants. At baseline and during the final peer support session, participants will have the option of completing data collection forms on paper, using iPads available at each study site or using another digital device. Data from paper forms will be entered into the REDCap database by the practice manager, practice nurse, or research officer. Paper data collection forms will be audited against online data at the end of the study for accuracy and completeness. All data collection forms are available on request.

**Table 1 Tab1:** Evaluation schedule with RE-AIM framework domains

RE-AIM Domain	Measure	Evaluation process
Reach	Number of people living with mental health conditions referred to the project	Analysis of routinely collected process data
	Characteristics (i.e., age, gender, diagnosis, treatment) of those who consent to participate vs. those who did not	
Effectiveness		
*Primary*	Participant self-efficacy (GSE)	Collected at enrolment (-t_1_) or baseline (t_0_) 3, 6, 9 months (t_1_ to t_3_) post-baseline
*Secondary*	Patient psychological distress (K10) Participant personal recovery (RAS-DS) Cost-effectiveness (EQ-5D-5L)	
	Family member or carer burden (BSFC-s) Peer worker self-efficacy (GSE)	Collected pre- (t_0_) and post-intervention (t_1_)
	Participant satisfaction with service (YES^a^) Practice staff attitudes towards peer workers^b^ Participant service use costs^c^ Perceived effectiveness of trial^b^	Collected post-intervention (t_1_) only
Adoption	Perspective of participants, family members and carers, peer workers, and practice staff	Semi-structured interviews and focus groups Analysis of routinely collected process data
Implementation	Frequency and content of participant-peer worker encounters	
Maintenance	Feedback from participants, family members and carers, peer workers, and practice staff	

^a^Short-form adjusted for CMOs

^b^Measure (Likert scale) developed for the study, in (TFA)

^c^Self-report questionnaire of service use and associated costs

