### Health outcomes and health services utilisation

Quality of life years: The European Quality of Life 5-Dimension 5-Level scale (EQ-5D-5L) [35] is a reliable (*α* = 0.82), validated, 5-item multidimensional measure commonly used in the field of health economics to estimate the number of quality-of-life-years resulting from an intervention to predict future costings. Respondents indicate which statement they agree with most regarding their health ‘today’ for five health domains with lower scores indicating better health. Respondents also provide an indicator of their general health on a scale of 1–100 (higher scores indicate better health). This measure will be used to inform the intervention efficacy in terms of prospective healthcare cost-reduction at baseline, 3 months post-baseline, 6 months post-baseline, and 9 months post-baseline.Healthcare service use.A 12-item questionnaire developed for this study will be used to collect information about participant health resource use. The questionnaire is specific to the socio-economic status of participants and costs incurred from accessing services and treatments (e.g., service and treatment costs). This measure will be used to provide context to findings around intervention efficacy in terms of healthcare costs at baseline, 3 months post-baseline, 6 months post-baseline, and 9 months post baseline.Burden experienced by family members or carers: The Burden Scale for Family Caregivers (BSFC-s) [36, 37] is a widely used reliable (*α* = 0.92), validated, ten-item unidimensional self-report measure of subjective carer burden amongst family caregivers. Responders indicate agreement with statements on a scale from 0 (strongly disagree) to 3 (strongly agree), with total possible scores of 0–30 (lower scores indicate lower carer burden). This measure will be used to inform intervention efficacy in terms of ongoing effects for participating family members or carers at baseline, 3 months post-baseline, 6 months post-baseline, and 9 months post-baseline.

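### The carer-burden sample has no stated minimum age or caring role, although its scale measures burden among family caregivers

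*Protocol article*

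**What the plan says.** The Eligibility criteria section of the protocol article sets a minimum age of 18 and other conditions for patients. A separate paragraph then deals with the carer sample: "a subset of family members or carers will complete the short-form Burden Scale for Family Caregivers (BSFC-s". On how they are found, it says: "Participants who are willing and have a suitable person to nominate will be provided with a consent form, questionnaire, and reply paid envelope", which the participant passes on. Entry is by post or online link: "Family members and carers can opt in to be part of the study at this point by either returning the completed forms". The paragraph closes with the rule at issue: "No inclusion or exclusion criteria apply beyond being nominated by the participant".

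The section on health outcomes and health services utilisation describes the BSFC-s as a "self-report measure of subjective carer burden amongst family caregivers", scored 0 to 30 with lower scores meaning less burden. Table 1 lists it as a secondary effectiveness measure, and the Abstract plans for approximately 150 respondents. The Discussion says that family members and carers involved in the participant's care may benefit because the trial reduces the support they give.

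**The concern.** The eligibility rule does not match the outcome it feeds. The scale and the expected mechanism both presuppose someone who provides support. The rule asks only for nomination, and the group is family members *or* carers, so a relative with no caring role qualifies. Such a person has no support to reduce. If their score does not move, they pull the average change in burden toward zero, and a real benefit to carers could be understated.

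The second issue is protection of respondents. The age limit of 18 appears in the patient list only, and the carer paragraph says that no further criterion applies. A participant's teenage child is therefore a permitted nominee. Patients are screened by a GP and give consent through a practice nurse. Nominees receive their consent form from the participant, and the article describes no age check on that route.

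**Working it through.** The documents give no effect size, standard deviation or power for the carer sample, so there is no stated figure to reproduce. The check is a comparison of the text, followed by an illustration of dilution.

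**Text comparison**

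| Question | What the protocol article says | Where |
|---|---|---|
| Who may be nominated? | A suitable family member or carer; suitable is not defined | Eligibility criteria |
| What else is required? | Nothing beyond nomination | Eligibility criteria |
| Is there an age limit? | 18 or older, in the patient list only | Eligibility criteria |
| Whom does the scale describe? | Family caregivers | Health outcomes and health services utilisation |
| How would they benefit? | By providing less support | Discussion |
| When is the first measure? | Before the intervention (t0), or at baseline | Table 1; Health outcomes and health services utilisation |

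The first three rows admit people outside the group described in the fourth and fifth. The last row shows that timing is a different matter. Table 1 has "Collected pre- (t_0_) and post-intervention (t_1" and the outcome text has "ongoing effects for participating family members or carers at baseline, 3 months post-baseline, 6 months post-baseline, and 9 months post-baseline". These differ on the later assessments, which is a separate inconsistency to reconcile, but both place the first measure at or before the start of support.

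**Dilution (illustration)**

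Assumptions: a share f of respondents has no caring role, their true change is zero, and the spread of the change scores is unaffected. None of these comes from the documents.

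- Observed mean change = (1 − f) × change among true carers.
- Sample size needed for the same power is multiplied by 1/(1 − f)².

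| f | Mean change multiplied by | Required N multiplied by |
|---|---|---|
| 10% | 0.90 | 1/0.90² = 1.23 |
| 20% | 0.80 | 1/0.80² = 1.56 |
| 30% | 0.70 | 1/0.70² = 2.04 |

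At f = 20%, 150 respondents carry about the information of 150 × 0.80² = 150 × 0.64 = 96 carers. On the score scale, an assumed true fall of 2 points would be seen as 2 × 0.80 = 1.6.

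**The case against.** The strongest reply is that the pool is narrower than the closing sentence suggests. The paragraph speaks of family members or carers and of a suitable nominee, and the Discussion refers to those involved in the participant's care. A reader might infer that anyone at all can join; the text does not support that. But suitable is left to the participant's judgement, and being family does not imply giving care, so the gap narrows without closing.

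It can also be said that a journal article condenses the full protocol. That does not help here, because the sentence states that no criteria apply. A role or age criterion elsewhere would contradict it. The consent form is not shown, however, so its wording on age cannot be judged, and the article does not say that staff never speak to nominees.

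A broad family sample is defensible for the stated aim of learning about impact beyond the participant. Relatives without a formal caring role may also report some subjective burden, so zero change among them is an assumption. That limits the dilution argument to a possibility.

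Two stronger readings are tempting. One is that people first measured after support began will enter as baseline respondents. The eligibility sentence says nothing about timing, and the planned first measure is at t0 or baseline. A return cut-off for posted forms is operational detail that an article may leave out. The other is that enrolled patients should be barred from acting as nominees. A patient may also be a genuine carer, and the documents show no harm from allowing it.

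**Conclusion.** The point holds in limited form. The protocol expressly applies no age or caring-role criterion to respondents on a caregiver-burden scale, and that does not fit the scale or the expected mechanism. The documents permit relatives who give no support, and minors, to enter; they do not show that either will happen or how often.

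The size of any bias is unknown. The multiplier 1 − f is exact only if non-carers show no change, and f is not given. The information loss also assumes an unchanged spread of scores. The consequence is confined to a secondary outcome in a voluntary subset. The BSFC-s is not among the continuous outcomes named as examples in Statistical methods, and the primary General Self-Efficacy comparison is untouched. The age gap merits correction however rarely it would arise.

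**What to change.** Replace the closing sentence of the carer paragraph with a rule to this effect: *the nominee is 18 or older and is currently involved in supporting the participant*. Confirm both by tick-boxes on the existing consent form, so that neither a new visit nor a new instrument is needed.

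The cost is a minor ethics amendment and a small form change. Somewhat fewer than 150 respondents would result, including the loss of any carers under 18; the others lost would be mainly people the scale was not designed to measure. Checking the date of the first BSFC-s against the first peer-support session is an optional operational addition.

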## Intervention

Each participant allocated to the intervention will be matched by a ‘peer coordinator’ (a champion peer worker coordinating between peer workers and the study staff) to the skills and experience of a peer worker. The main intervention steps and the flow of health care providers can be seen in Fig. 2.

**Fig. 2 Fig2:**
[figure not shown]
Intervention stages and flow of care

The initial meeting between the participant and peer worker will provide an opportunity to refine and mutually agree on the support plan. Support may entail emotional and practical assistance, phone calls, home visits, community linkage, and sharing of strategies to enhance lifestyle behaviour (e.g., social connection, physical activity, stress management) to build self-efficacy and self-care and to set recovery goals.

Peer workers will provide 8–12 h of support per participant over approximately 2–3 months, with the option to extend for 2–3 months if needed. If desired, participants may also cease receiving peer worker support sessions prematurely, if they feel they have gained sufficient benefit from these sessions. At the completion of the intervention, the peer worker and participant will identify supports that are relevant and available and the peer worker will link the participant with those supports. The peer worker will provide a summary of trial activities to the participant and their GP. This is intended to be used for discussion in a primary care appointment to facilitate ongoing continuity of care.

## Data collection

A timeline for the collection of data can be seen in Fig. 3.

**Fig. 3 Fig3:**
[figure not shown]
Schedule of enrolment, intervention, and assessment (SPIRIT Figure)

A summary of the evaluation schedule, underpinned by the RE-AIM framework is provided in Table 1. Routinely collected data including demographics and diagnosis details will be recorded (with consent) by practice staff through chart auditing the GP records of prospective participants. At baseline and during the final peer support session, participants will have the option of completing data collection forms on paper, using iPads available at each study site or using another digital device. Data from paper forms will be entered into the REDCap database by the practice manager, practice nurse, or research officer. Paper data collection forms will be audited against online data at the end of the study for accuracy and completeness. All data collection forms are available on request.

**Table 1 Tab1:** Evaluation schedule with RE-AIM framework domains

RE-AIM Domain	Measure	Evaluation process
Reach	Number of people living with mental health conditions referred to the project	Analysis of routinely collected process data
	Characteristics (i.e., age, gender, diagnosis, treatment) of those who consent to participate vs. those who did not	
Effectiveness		
*Primary*	Participant self-efficacy (GSE)	Collected at enrolment (-t_1_) or baseline (t_0_) 3, 6, 9 months (t_1_ to t_3_) post-baseline
*Secondary*	Patient psychological distress (K10) Participant personal recovery (RAS-DS) Cost-effectiveness (EQ-5D-5L)	
	Family member or carer burden (BSFC-s) Peer worker self-efficacy (GSE)	Collected pre- (t_0_) and post-intervention (t_1_)
	Participant satisfaction with service (YES^a^) Practice staff attitudes towards peer workers^b^ Participant service use costs^c^ Perceived effectiveness of trial^b^	Collected post-intervention (t_1_) only
Adoption	Perspective of participants, family members and carers, peer workers, and practice staff	Semi-structured interviews and focus groups Analysis of routinely collected process data
Implementation	Frequency and content of participant-peer worker encounters	
Maintenance	Feedback from participants, family members and carers, peer workers, and practice staff	

^a^Short-form adjusted for CMOs

^b^Measure (Likert scale) developed for the study, in (TFA)

^c^Self-report questionnaire of service use and associated costs

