## Primary outcome measures

The primary outcome will be change in a person’s self-efficacy measured by the GSE [32]. The GSE is a reliable (*α* = 0.76 to 0.90), validated, ten-item unidimensional self-report scale used to assess self-efficacy within general adult populations. The scale conceptualises self-efficacy as a person’s perceived ability to cope and adapt in the face of both daily hassles and more stressful life events. Respondents indicate how much a given item applies to them from 1 (not at all true) to 4 (exactly true), with total possible scores of 10–40 (higher scores indicate greater self-efficacy). The scale was originally designed to assess change occurring over the course of a trial and is also used in CMO contexts as an indicator of client well-being. This tool will be used to inform intervention efficacy for participants at baseline, 3 months post-baseline, 6 months post-baseline, and 9 months post baseline. For all measures taken at multiple time points, the comparison between care as usual (baseline) and post-intervention (3 months post-baseline) will be of primary importance, whilst following time points will inform the longevity of any intervention-related effects.

All baseline measures, including the GSE, will be administered as a questionnaire by a practice nurse following screening and consent procedures. During the final session of peer support, the peer worker will assist the participant with completing the 3-month post-baseline measures. All further follow-up measures will be administered as a questionnaire either through REDCap or a telephone call from study staff depending on participant preference.

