## Secondary outcome measures

### Efficacy

Psychological distress: The Kessler Psychological Distress Scale (K10) is a reliable (*α* = 0.93), validated, 10-item unidimensional self-report measure of participant mental distress [33] often used by clinicians as a screening tool and marker of eligibility for government-funded support services. Respondents indicate from 1 to 5 how much a given statement was true for them in the past 4 weeks with total possible scores of 10–50 (lower scores indicate less distress). The GP or a study nurse will administer the K10 to potential participants as a screening material to aid in confirming eligibility, and then at 3 months post-baseline, 6 months post-baseline, and 9 months post-baseline.Personal recovery: The Recovery Assessment Scale—Domains and Stages (RAS-DS) [18] is a reliable (*α* = 0.96), validated, 38-item multidimensional self-report measure of personal recovery designed to measure the recovery-oriented impact of services provided to participants. The scale is constructed of five domains relevant to recovery goals, with respondents indicating how much a given statement is true for them from 1 to 4. Higher scores in each domain or stage indicates areas the person feels more confident about as part of their recovery. The RAS-DS is routinely used by peer workers as a descriptive tool. This tool will be used to inform intervention efficacy for participants at baseline, 3 months post-baseline, 6 months post-baseline, and 9 months post-baseline.Satisfaction with service: The Your Experience of Service (YES) is a descriptive short-form (21-item) version of the Australian YES [34] tailored to evaluating CMOs. The YES is used in evaluating services delivered by government and non-government healthcare providers in Australia. Respondents indicate their experiences from 0 to 5 across three areas (higher score indicates more satisfaction with a service). The measure then prompts responses to open-ended questions for further information. This measure will be completed during the participant’s final session.

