### Evaluation of intervention

Stakeholders from a range of perspectives (participants, peer workers, family members or carers, and practice staff) will be invited to take part in evaluating the intervention in terms of efficacy and acceptability.Effectiveness and acceptability.Perceived effectiveness of intervention will be measured using a scale adjusted for this purpose. This scale will follow the generic form of the TFA acceptability questionnaire, which is an eight-item theory-informed self-report measure of the acceptability of healthcare interventions [31]. Constructs consider affective attitudes, burden, ethical consequences, perceived effectiveness, coherence, self-efficacy, opportunity costs, and overall acceptability of an intervention. Responders indicate agreement with statements on a scale from 1 to 5, with total possible scores of 8–40 (higher scores indicate higher acceptability). This measure will be completed during the participant’s final session.Attitude toward peer workers.Practice staff attitude toward peer workers will be measured using the affective attitude item from the generic form of TFA acceptability questionnaire, which asks either ‘Did you like or dislike [intervention]?’ (participants indicate from 1 (strongly dislike) to 5 (strongly like)) or ‘How comfortable did you feel [behaviour e.g., to engage with] [intervention]?’ (participants indicate from 1 (very uncomfortable) to 5 (very comfortable)) where [intervention] refers to peer workers [31]. This measure will be completed after the final participant has completed the intervention.Qualitative assessment.Approximately 6 months after the PS-PC has launched, all participants will be invited via email to take part in interviews of approximately 30 min in length. Peer workers and practice staff will also have the option of participating in a focus group of approximately 1.5 h. Interviews and focus groups will follow a guide developed in reference to CFIR and RE-AIM frameworks. Verbal informed consent will be obtained by the administering study staff member prior to the start of each interview and focus group.

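### Satisfaction (YES) and acceptability (TFA) are rated with the peer worker's help in the final session, so both scores are at risk of an upward bias that the schedule cannot reveal

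*Protocol article*

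**What the plan says.** Four parts of the protocol article bear on this.

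- **When the forms are completed.** For YES, Secondary outcome measures (Efficacy) says: "The measure then prompts responses to open-ended questions for further information. This measure will be completed during the participant’s final session". For the participant TFA scale, Evaluation of intervention has the same instruction: "with total possible scores of 8–40 (higher scores indicate higher acceptability). This measure will be completed during the participant’s final session".
- **Who is there.** Primary outcome measures says: "During the final session of peer support, the peer worker will assist the participant with completing the 3-month post-baseline measures".
- **How often.** Table 1 gives participant satisfaction and perceived effectiveness the entry "Collected post-intervention (t_1_) only".
- **What is rated, and by whom it is provided.** The protocol describes YES this way: "The Your Experience of Service (YES) is a descriptive short-form (21-item) version of the Australian YES", and adds that it is "tailored to evaluating CMOs". Study design and setting states that the CMOs employ the peer workers.

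On handling, Data collection says of paper: "Data from paper forms will be entered into the REDCap database by the practice manager, practice nurse, or research officer". It also offers site iPads or another device, and an end-of-study audit of paper against online data. Randomisation says that "staff leaders at the relevant practice site will champion the practical implementation of the PS-PC".

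**The concern.** A participant who has spent several hours with an individually matched peer worker is asked, in their last meeting and with that worker helping, how good the service was and whether the intervention was acceptable. Critical answers are harder to give in that setting than in private, so the plausible direction of any distortion is towards better scores.

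The secondary objective is feasibility and the barriers to implementation. Unfavourable ratings are the most informative evidence for that objective, and they are the ones this procedure is most likely to discourage. Statistical methods nevertheless lists YES and TFA among the continuous outcomes for linear models, so the scores will be reported as quantitative results.

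A smaller worry is who reads the paper forms afterwards. YES includes free-text answers, and the practice manager or nurse may key them at a practice whose leaders promote the intervention.

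**Working it through.** The protocol states no figure for this point, so there is none to reproduce. The check sets the passages side by side.

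1. **Is the peer worker's help meant to cover YES and TFA?** Table 1 defines t1 to t3 as 3, 6 and 9 months, so t1 is the 3-month point. YES and perceived effectiveness are placed at t1. Primary outcome measures has the peer worker help with the 3-month measures in the final session, and the sections on YES and TFA each name that session. No passage excepts these two forms. The natural reading is that the help covers them.

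2. **Does the helper belong to what is being rated?** YES is tailored to CMOs and CMOs employ the peer workers, so the helper works for the rated service. The TFA scale rates the intervention, which the helper delivered.

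3. **Could a shift be seen or cancelled?** That would need a baseline, a usual-care reading or a later reading taken another way. Table 1 gives none for either form. The 6- and 9-month contacts, by REDCap or telephone, do not include them.

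4. **Do the stated safeguards remove the peer worker's influence?**
   - Device choice: Data collection offers it during the final peer support session, so the worker is still present.
   - Study identifiers: these de-identify the dataset, but do not hide an answer from someone in the room.
   - Paper-to-online audit: this finds keying errors, not answers shaped before they were written.

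5. **Who may see paper forms?** The practice manager, practice nurse or research officer. Peer workers and CMO staff are not listed. Practice staff have an interest in the intervention, but YES does not rate them.

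6. **Scale, as illustration only.** Suppose a share p of respondents scores one category higher than they would in private. The mean of a 0–5 YES item then rises by p. For an assumed p of 0.25 to 0.50 that is 0.25/5 = 5% to 0.50/5 = 10% of the item range. If the same happened on four of the eight TFA items, the total would rise by 4 × 0.25 = 1 to 4 × 0.50 = 2 points. On a range of 40 − 8 = 32 that is 3.1% to 6.3%. Both p and the number of items are assumptions, so these figures translate a supposed shift and do not estimate one.

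**The case against.** The best case against this point has several parts.

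- **Data entry.** A reader might infer from the data-entry sentence that the people being rated handle the answers. The text does not support that: it names practice staff or the research officer, and YES evaluates the CMO. Paper is also optional, and identifiers and an audit are in place. The objection stands, and it reduces data entry to a confidentiality matter.
- **A verdict on a named person.** A reader might also infer that participants must judge a named individual. They are not asked to: YES concerns a service and the participant TFA scale concerns the intervention. The TFA item that refers to peer workers is for practice staff.
- **Silence in an article.** The forms and the data management procedures are available on request, and may contain privacy instructions. That weakens any argument from the absence of a sealed-return route. The reply-paid envelope for carers may also be simple logistics. But the main point does not rest on silence, because the peer worker's help in the final session is stated outright.
- **Other evidence.** YES is called descriptive, both measures are secondary, and about 60 interviews and six focus groups also explore acceptability. Criticism therefore has another outlet. This limits the consequence but does not correct the scores.
- **Completeness.** Collection in the final session protects response. That is a real advantage, and the fix should keep it where it can.

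**Conclusion.** The concern holds as a risk. As written, the procedure has participants complete YES and the TFA scale with help from the worker who delivered what they are rating, at a single time point with no comparison reading. Upward social-desirability bias is plausible and could not be detected from the data planned. Its size is unknown.

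It would be tempting to say that the scores will be biased upward. The documents do not support that certainty, because they contain nothing on how participants answer with and without the worker present. The conclusion assumes only that the worker's help extends to all forms completed in that session, as the text reads.

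The confidentiality of paper forms is a secondary matter. Neither point changes the sample size. The worker's help with the 3-month GSE is a separate question, not judged here. This is a low-cost improvement to two secondary outcomes.

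**What to change.** In Primary outcome measures, Secondary outcome measures (Efficacy) and Evaluation of intervention, state that YES and the participant TFA scale are completed without the peer worker's assistance or presence. The participant may use the iPad or their own device in private at the end of the final session, a REDCap link, or paper sealed for the research officer.

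In Data collection, allow only the research officer to enter paper versions of these two forms. Tell participants that the peer worker, the CMO and the practice will not see individual answers. Data privacy and management sends participant forms to the coordinating site at study completion, so these two paper forms need a sealed route of their own to the research officer.

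The cost is a few sentences and some envelopes, which are already used for carers. The drawback is that some forms may not come back. Private device completion before the participant leaves limits this, as do reminders through the REDCap or telephone contact already planned for later follow-ups.
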